#### Secondary endpoints

The economic effects of full implementation of PFR compared to standard treatment in treating and preventing FI in patients after LAR will be determined by a cost effectiveness analysis. This will be evaluated by regression analysis (*see* subheading “cost effectiveness analysis” below for detailed methods).The effect of the demographic, surgical, and oncologic parameters on the development of FI after LAR relative to PFR and standard treatment will be explored.The effect of PFR compared to standard treatment on anorectal outcomes in patients after LAR by the DeFec, LARS score, and defecation log will be determined.The effect of PFR compared to standard treatment on QoL by means of the Fecal Incontinence Quality of Life (FIQL), EORTC Colorectal Quality of Life Questionnaire QLQ-CR29, and EQ5D will be determined. The latter evaluation will be used for economic evaluations in particular.

The dependent variable is the degree of QoL/anorectal outcome. The independent variable is the intervention or the standard treatment. The difference between the effect in the intervention group and the control group will be analyzed by analysis of covariance (ANCOVA) as well. No additional analyses, such as subgroup analysis, are written out in advance.

#### Intention to treat and per protocol analysis

Primary study outcome will be based on intention to treat analysis. In addition, per protocol analysis will be performed. This analysis will be done to avoid the effects of crossover, protocol violation, and dropout.

#### Handling and storage of data and documents

The anonymized data will be stored in Castor EDC. Only the coordinating and principal investigators will have access to the key of the code that matches participants to study data. Most patients will fill in their questionnaires themselves online. Only those without email will fill in the paper version of the questionnaires.

No specific plans, besides an active attitude towards the participating centrums, are made to promote participant retention and complete follow-up. If patients fail to start/continue their allocated intervention (Pelvic Floor Rehabilitation, since failure of control group is not possible), data will be collected according to the study protocol for use in per protocol analysis.

### Sample size calculation

Recent studies reported an improvement of FI after LAR by PFR of five points on the Wexner-score (SD = 8) [11, 12, 15]. This improvement is considered to be of great clinical significance.

In the original design of this trial, an independent T-test was suggested for the primary outcome measure. Progressive insights made it possible to make a change to the ANCOVA analysis, since this test reduces the within-group error variance. Therefore, the precision of the treatment estimate has been increased, and the length of the confidence interval has been reduced [18]. Therefore, for this trial with an ANCOVA as primary statistical test, the following sample size calculation was made:
The T-test sample size was based on 80% power to detect a difference of five points in the Wexner score, SD = 8, two-grouped t-test, with a 0.05 two-side significance level: 63 patients per arm.The sample size calculation for analysis of covariance (ANCOVA) in randomized clinical trials described by Borm et al. [18] was used, with an estimated correlation factor (R) of 0.5. The required sample size is 32 patients per arm.Assuming a withdrawal/replacement rate of 50% [11, 12, 15], a total of 128 patients should be randomized.

### Data monitoring, harms, and auditing

The Committee on Research Involving Human Subjects, Arnhem-Nijmegen approved this study and declared it as a “negligible risk” study. Therefore, no Data Safety Monitoring Board is needed, and no interim analysis or formal stopping rules for the trial are needed to be conducted or formulated. No anticipated harms exist, nor will compensation be provided for trial participation. No need for post-trial care is expected. Monitoring will occur with a frequency of one visit per year per center, in which the following items will be checked: informed consents, availability of data in Trial Master File and Investigator Site Files, inclusion and exclusion criteria, SAEs, and source data verification. Trial auditing will be twice a year since that is the frequency of meeting with the Trial Steering Group of principal investigators. Any solicited and spontaneously reported adverse events and other unintended effects of the trial will be reported to the Committee on Research Involving Human Subjects, Arnhem-Nijmegen, who will review the situation and give appropriate advice regarding expectedness, seriousness, severity, and causality.

### Patient information and questionnaires

#### Medical history/patients characteristics

The patient information will include the medical history, gender, age, tumor height (MRI and scoping), height and type of the anastomosis, type of surgery (laparoscopic, open or robotic), construction of a temporary stoma, peri- and postoperative complications, time of surgery, blood loss, time of hospitalization, and clinical and pathological TNM staging.

#### Groningen defecation and fecal continence (DeFeC)

This questionnaire incorporated various Rome IV criteria and scoring tools for severity of constipation and fecal incontinence. Overall reproducibility of the Groningen DeFeC questionnaire is acceptable and its validity is good [19]. This makes it a feasible screening tool for defecation disorders. The primary outcome, the Wexner score, will be derived from this questionnaire. The distribution of subtypes and symptoms of fecal incontinence in the general Dutch population has already been investigated with the use of this questionnaire [20].

#### Wexner incontinence score

The Wexner score allows the severity of fecal incontinence to be assessed using five questions (Table 2). The minimal score patients can obtain is 0 (continent), and the maximum score is 20 (highest severity of incontinence). This score describes the type and frequency of the incontinence and impact on daily life. No data exist about the internal consistency and the criteria/content validity of this score. The intraclass correlation coefficient (ICC) of the Wexner score is good to excellent (ICC 0.75). The construct validity is R(Pearson) = 0.78 (correlation with Vaizey score) [21]. The Wexner score has an important association with the Fecal Incontinence Quality of Life score (r = − 0.45), but a weak correlation with changes in the EQ-5D has been described [22].

**Table 2 Tab2:** Wexner incontinence score

Type of incontinence	Frequency				
	Never	Rarely	Sometimes	Usually	Always
Solid	0	1	2	3	4
Liquid	0	1	2	3	4
Gas	0	1	2	3	4
Wears pad	0	1	2	3	4
Lifestyle alteration	0	1	2	3	4

Never, 0; rarely, < 1/month; sometimes, < 1/week, ≥1/month; usually, < 1/day, ≥1/week; always, ≥1/day

0, perfect; 20, complete incontinence

#### LARS score

The LARS score is a validated scoring system for bowel dysfunction after low anterior resection for colorectal cancer. The Dutch version was recently validated [23]. This score covers the five most bothersome issues in terms of prevalence and impact of QoL, namely incontinence for flatus and liquid stool, frequency, clustering, and urgency. Scores range from 0 to 42, with subdivisions in three categories: no (0–20), minor (21–29), and major LARS (30–42). A statistically significant association exists between a higher LARS score and an impaired QoL. The test-retest reliability of the LARS score is good, with an interclass correlation coefficient of 0.79 [23].

#### Fecal incontinence quality of life score (FIQL score)

The FIQL score is a condition-specific questionnaire on quality of life and consists of four multi-item subscales: lifestyle (10 items), coping/behavior (nine items), depression/self-perception (seven items), and embarrassment (three items), for a total of 29 items [24]. Each item has four answer opportunities, with a score of 1 to 4, where 1 indicates a low quality of life and 4 a high quality of life.

The internal consistency (Cronbach’s α) is good (subscale 1, 0.96; subscale 2, 0.96; subscale 3, 0.88; and subscale 4, 0.80). The total FIQL has an adequate internal and external responsiveness (standardized response mean = 0.5, r = − 0.48, and area under the curve = 0.765). The intraclass correlation coefficient is good to excellent: 0.80 (embarrassment) to 0.93 (lifestyle) [25].

#### EORTC colorectal quality of life questionnaire QLQ-CR29

Quality of life will be measured by the EORTC Colorectal Quality of Life Questionnaire QLQ-CR29. The ICC of the QLQ-CR29 is good to excellent (Intraclass Correlation Coefficient: 0.78) [26, 27]. The Internal consistency of this questionnaire reaches the criterion of 0.70 [26].

#### Defecation and urinary log

This log provides insight into the defecation pattern, type of consistency (Bristol Stool Form Scale) [28], feeling of urge to defecate, episodes of fecal incontinence, and the use of diapers. Also, the use of medication will be noted. The patient will keep up this log 5 days per week after LAR or temporary stoma from the moment of randomization until the end of the intervention (3 months). This log will be used to allow discussion about the number of treatment sessions that will be needed to obtain an effect of PFR. Fecal incontinence occurs often in combination with incontinence for urine. In case of urine incontinence, the patient has to keep up the severity and episodes of this urinary incontinence. The incontinence will namely influence the costs (i.e., use of diapers).

### Cost effectiveness analysis (CEA)

The economic evaluation investigates, alongside the clinical trial, the value for money of full implementation of the standardized pelvic floor rehabilitation program compared to the usual care. This will be done from a societal perspective. The timeframe of empirical evaluation is 6 months. The effect at 6 months is supposed to be sustainable for 5 years, which will be explored by decision-analytic modelling. The design of the economic evaluation follows the principles of a cost-utility analysis and adheres to the new Dutch guideline for performing economic evaluations in health care (ZINL, 2015). Fecal incontinence-related problems are anticipated to decrease after PFR, which would result in a reduction of health care consumption, increased work resumption/participation, and an increase in health-related quality of life in this target population. Cost-effectiveness will be expressed in terms of gains in the cost per Quality Adjusted Life Year (QALY). Uncertainty will be dealt with by one-way sensitivity analysis (deterministic) and by parametric statistics, ultimately presenting cost-effectiveness acceptability curves. The modelling part will be probabilistic.

#### Cost analysis

The cost analysis exists of two main parts. First, at the patient level, the volume of care will be measured prospectively over the time path of the study using patient-level diaries (on fecal incontinence-related health care consumption), completed, if necessary, by data from the patient training facility’s administration system. The diary will be developed in a way that it structures and makes uniform the health care consumption of a fecal incontinent patient for this particular target population. Second, per item of health care consumption, the standard cost will be determined using the guideline for performing economic evaluations (ZINL, 2015), which will be completed with the total costs of items via activity-based costing. Productivity losses for patients will be assessed using a patient-based diary complemented with an interview on a 3-month recall basis between the researcher and the patient (at baseline and at the 3- and 6-month follow-ups). The friction cost-method will be applied following the Dutch guidelines (ZINL, 2015). In addition, travel time to the training site and related costs will be considered (also on the basis of the diary). Differences in costs between both groups will be evaluated using regression-based techniques.

#### Patient outcome analysis

The effect analysis adheres to the design of the randomized controlled trial and measures at baseline and at fixed points along time path/follow-up of the clinical trial (see design clinical trial). For measurements on the quality of the health status of the patients, a validated so-called health-related quality of life (HR-QoL) instrument—the EuroQol-5D (EQ-5D) [29]—will be used. This HR-QoL instrument will be completed by the patients and is available in a validated Dutch translation. The EQ-5D-5 L which is used in this study is a generic HR-QoL instrument comprising five domains: mobility, self-care, usual activities, pain/discomfort, and anxiety/depression [30, 31]. The EQ-5D-5 L index is obtained by applying predetermined weights to the five domains. This index gives a societal-based global quantification of the patient’s health status on a scale ranging from 0 (death) to 1 (perfect health). Patients will also be asked to rate their overall HR-QoL on a visual analog scale (EQ- 5D VAS) consisting of a vertical line ranging from 0 (worst imaginable health status) to 100 (best imaginable). For the EQ-5D-3 L, the version used before the introduction of the EQ-5D-5 L, a weak correlation was known to exist with changes on the Wexner score [22]. The same can be expected from the EQ-5D-5 L.

#### Budget impact analysis (BIA)

BIA will be conducted to assess how healthcare budgets will be influenced when offering the standardized pelvic floor rehabilitation program. This program is anticipated to allow savings of €191 in direct medical cost and €280 in productivity gains for the average patient on a yearly basis. The patient-based budget impact will be extrapolated to the population level. Although the BIA relies heavily on the findings from the economic evaluation described above, it will be conducted from various perspectives, such as from the broader perspective of the public purse down to the narrow healthcare perspective. To that end, use will be made of a health economic (decision analytical) model in which uncertainty will be taken into account. Deterministic uncertainty concerning BIA input, such as perspective, pricing parameters, time horizon, uptake, etc., will be dealt with by generating the budget impact as a series of sensitivity analyses covering a relevant range of costs. In general, for the BIA we adhere to the new guideline for performing economic evaluations in health care (ZINL, 2015).

### Investigational treatment

#### The control group

Patients in the control group will get the standard treatment that currently is used in daily practice. This standard treatment for postoperative FI consists of the prescription of bulking agents (i.e., Metamucil, psyllium fibers, Volcolon, or Normacol). Bulking agents can be beneficial to the consistency of the stool and therefore diminish soiling problems. These bulking agents may be used once or twice per day depending on the severity of FI. Standard oncologic follow-up after LAR at the surgical outpatient clinic will be provided. In case of severe FI and/or failing of standard treatment, cross over to the intervention group will be allowed. After finishing their allocated control group period, these patients with severe complaints might wish to undergo PFR. This will be allowed, and these patients will receive PFR according to the study protocol. After 12 sessions, patients will be asked to fill in another questionnaire, which will allow them to evaluate whether the length of the post-operative period after which PFR has been applied, influenced the patient’s outcomes.

#### The intervention group

Treatment of patients in the intervention group will consist of four modalities of pelvic floor rehabilitation in addition to the standard treatment:

1) pelvic floor muscle training to a) increase the maximum strength of muscle contraction, b) extend the time of muscle contraction, and c) improve the coordination of contraction of the pelvic floor muscles; 2) biofeedback, which is a behavioristic therapy that allows the patient to become conscious of the contraction and relaxation of the pelvic floor muscles and uses an anal electromyography probe; 3) electrostimulation, which can improve the effectiveness of the contraction strength of the pelvic floor muscles and uses the same anal electromyography probe as used for biofeedback; and 4) training with a rectal balloon to simulate the urgency to defecate, which is a method that enables the patients to train to retain stool, enabling the patient to retain a larger stool in the rectum.

The intervention will be performed by specialized pelvic floor physiotherapists, registered in the Dutch KNGF-NVFB register. These physiotherapists will be chosen based on the location of their practices. For the comfort of patients included in this study, the close location of the practices to the participating hospitals is important. Therefore both hospital-based and private practices were allowed to participate. The physiotherapists will be obliged to attend a course during which the treatment protocol and the case report form will be explained. The coordinating investigator will guide this course and will train the physiotherapists. During this training session, the correct way of digital rectal examination to assess the function of the pelvic floor, the use of biofeedback, electrostimulation, and the rectal balloon will be explained and illustrated using videos. An internationally accepted protocol, The Pelvic Floor Assessment Protocol, will be used for the digital rectal examination performed by the physiotherapist (International Continence Society 2006, Messelink et al.). The physiotherapist will also be instructed on how to use the case report form and report any adverse events during the 12 sessions of PFR. Since a patient’s adherence to PFR is a common problem, an instruction on how to enlarge this adherence to therapy will be provided [21, 22]. The complete treatment trajectory for both the control and the intervention group will be recorded in a standardized protocol, which has already been developed by clinical experts in the field [8].

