### Flow of the FORCE trial

After surgery, eligible patients will be randomized for either a standardized pelvic floor rehabilitation (PFR) program or standard treatment, which is defined as current daily practice. Blinding for PFR is not possible. Randomization and data collection will be performed by the coordinating investigator. In concordance with the study flowchart (Fig. 1), these steps will be followed:
After giving informed consent, eligible patients will be included in the FORCE trial. In the beginning of the inclusion period, this inclusion was supposed to occur preoperatively with a baseline measurement before surgery as well (measurement 1, M1). Since this preoperative inclusion led to reduced numbers of inclusion due to an overload of information, postoperative inclusion was allowed as well.Questionnaires will be administered 3 months after LAR (measurement 2, M2) to patients without a temporary stoma. Based on the current reports, approximately 70% of patients undergoing LAR also receive a temporary stoma [16]. In these cases, the questionnaires will be administered 6 weeks after stoma closure (measurement 2, M2).Randomization will take place after completing the M2 questionnaires. Patients will then undergo either standard treatment or a standardized PFR program that includes the standard treatment for 3 months (12 sessions, once a week).After finishing the PFR program or 12 weeks of participation in the control group, questionnaires will be send again (measurement 3, M3, primary endpoint).Long-term follow-up will be completed at 1 year after bowel continuity (measurement 4, M4).

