##### Rectal balloon training

Rectal balloon training is used to simulate the need for defecation. During training, a rectal balloon (Ashley Rectal Balloon, Pelvitec) will be inserted into the neorectum (i.e., remaining part of rectum and distal colon). Subsequently, the balloon will slowly be inflated using a syringe, which is connected to the balloon. Patients will be asked to pay attention to their rectal filling sensations and once they feel a strong desire for defecation, an adequate contraction of the sphincter and puborectal muscle needs to be produced to retain the balloon. The awareness that also their neorectum can adapt fecal content and that therefore, after a short period of active sphincter/pelvic contraction, the urge for defecation will diminish will strengthen their confidence in fecal continence [32]. Rectal balloon training helps to control fear of FI and allows patients to tolerate larger volumes of stool in the neorectum. Rectal balloon training will not be started until the patients’ maximum pelvic floor functions is recovered. During the last three PFR sessions, this training will be part of the sessions anyway. Rectal balloon training will be combined with biofeedback.

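### Active adverse-event reporting is described only for the PFR therapist and only during the 12 sessions, so any comparison of harms between arms would be distorted by unequal ascertainment

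*Protocol article*

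**What the plan says.** Two places in the protocol article deal with adverse events.

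- **The intervention group.** In the description of therapist training, the physiotherapist is to be instructed to "report any adverse events during the 12 sessions of PFR". This names a reporter and a period, and it applies to PFR. Under Pelvic floor muscle training, the therapist completes a case report form at every weekly session.
- **Data monitoring, harms, and auditing.** "Any solicited and spontaneously reported adverse events and other unintended effects of the trial will be reported to the Committee on Research Involving Human Subjects". This sentence has no limit of arm or time. The yearly monitoring visit at each center covers, among other items, "inclusion and exclusion criteria, SAEs, and source data verification". The same section states "No anticipated harms exist, nor will compensation be provided for trial participation".

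The control group section gives control patients bulking agents and the usual oncologic outpatient follow-up, with no adverse-event instruction. Under Use of cointerventions, the surgeon is named next to the physiotherapist as someone who fills in the case report form, but for cointerventions and medication changes.

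On timing, balloon training starts once maximum pelvic floor function has recovered, and in any case: "During the last three PFR sessions, this training will be part of the sessions anyway". M3 follows directly on the 12-week period in both arms, and M4 is one year after bowel continuity.

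**The concern.** In an open-label trial, a therapist who sees one arm every week and is told to report adverse events will learn of more events than routine outpatient follow-up will in the other arm. Minor events show this most, because they seldom surface unless someone asks. A difference in recorded harms would then reflect how often patients were observed as well as what the treatment did. The distortion would probably run against PFR.

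The second gap is in time. Anal probes are used at every session and the balloon at the last three at least. A problem that appears after session 12 has no described active route into the trial data.

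The article hopes that positive results will support guidelines and reimbursement of PFR as standard care. A statement about harms relative to usual care would be expected alongside such results, and the capture as described would not support one.

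**Working it through.** The plan states no harms rate and no harms sample size, so there is no figure to reproduce. The check compares what is described for each arm, counts the timing, and sizes the possible distortion.

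**1. Capture described, by arm**

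| Route | PFR arm | Control arm |
|---|---|---|
| Named reporter told to report adverse events | Physiotherapist, at 12 sessions | None described |
| General rule on solicited and spontaneous reports | Yes | Yes |
| SAE check at yearly monitoring | Yes | Yes |
| Surgeon on case report form | Cointerventions, medication | Cointerventions, medication |

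The general rule says where reports are sent. It does not say who solicits them, from which arm, or when.

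The remaining instruments do not fill the gap as described. DeFeC, Wexner, LARS, FIQL, QLQ-CR29 and EQ-5D measure symptoms or quality of life. The log covers defecation, urinary incontinence and medication. The cost diary covers incontinence-related care, and the interviews cover productivity losses.

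**2. Timing**

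- Latest start of balloon training: session 12 − 3 + 1 = 10. At least 3/12 = 25% of sessions include it.
- From session 10 to session 12 at weekly spacing: 2 weeks. Balloon use and the reporting window end at the same session, so all supervised use is inside the window.
- From the end of the 12 weeks (2.8 months) to M4, if treatment starts at the nominal time:
  - without a stoma: 12 − 3 − 2.8 = 6.2 months;
  - after stoma closure, with 6 weeks = 1.4 months: 12 − 1.4 − 2.8 = 7.8 months.
- The 6-month cost interview is a contact within this follow-up, but it is described as covering productivity losses.

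**3. What can be said within the PFR arm**

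With n patients and no events, the exact one-sided 95% upper limit is 1 − 0.05^(1/n).

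- n = 64 (128 randomized, equal allocation assumed): 1 − 0.05^(1/64) = 4.6%.
- n = 32 (the required number per arm): 1 − 0.05^(1/32) = 8.9%.

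**4. Distortion between arms**

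Expected recorded events = n × true risk × capture proportion. With equal true risk, the apparent risk ratio is the ratio of the capture proportions, whatever that risk is. All risks and capture proportions below are assumptions; n = 64 per arm.

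| True risk, both arms | PFR, 90% captured | Control, 60% captured | Control, 30% captured |
|---|---|---|---|
| 5% | 2.9 | 1.9 | 1.0 |
| 10% | 5.8 | 3.8 | 1.9 |
| 20% | 11.5 | 7.7 | 3.8 |

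Apparent risk ratio: 0.90/0.60 = 1.5 and 0.90/0.30 = 3. With 90% capture in both arms it is 1.

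**The case against.** The article condenses protocol version 18, which is not shown. Who solicits adverse events, on which form and until when may be set out there. The sentence on the physiotherapist describes what one profession is taught, and does not say that no other route exists. This stands as a limit: the point concerns what the article describes. But the article has its own harms section and gives a specific instruction for one arm only. If version 18 has a symmetric procedure, a clarifying sentence is enough.

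A reader might infer that control events are not captured at all. The documents do not support that: the general rule accepts reports from either arm at any time, and SAEs are checked at every center. Nor are control patients without trial contact before M3, given the log, cost diaries and interviews.

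A reader might also infer that reporting stops just as balloon exposure begins. Session 10 is the latest start, and supervised balloon use ends with the window. Only delayed events are left out, and nothing in the article says that such events are expected.

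Finally, the article announces no between-arm analysis of harms. That also stands, so the distortion is conditional on such a comparison being made. The capture proportions are assumed, and the range shows how strongly the result depends on them.

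**Conclusion.** The point holds in limited form. As described, active adverse-event reporting belongs to one arm and one period. No matching active capture is described for control patients, and none in either arm for delayed events after session 12. Any between-arm comparison of harms would therefore mix treatment effect with ascertainment. Under the assumed capture proportions, the apparent risk ratio is 1.5 to 3 when the true ratio is 1. The true size is unknown because the documents give no capture or event rates.

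It would go too far to conclude that the statement on anticipated harms cannot be examined. It is an expectation that accompanies the negligible-risk classification, not a hypothesis of the trial, and harms during PFR can be bounded within that arm (4.6% for no events in 64, if those events are captured).

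**What to change.** - Add one identical adverse-event item to the M3 questionnaire already sent to both arms (what happened, when, any hospital contact or re-operation). Base any between-arm comparison of harms on that item.
- Report therapist-recorded events separately, as a listing for the PFR arm.
- Repeat the item at M4 for delayed events. Read it descriptively, with and without control patients who took PFR after M3, as the Primary outcome section already does for efficacy. M4 cannot carry a clean comparison because of these patients.
- State when adverse-event reporting ends, and reconcile the therapist instruction with the general rule under Data monitoring, harms, and auditing.

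The cost is an amendment and a slightly longer questionnaire, with no new visits. The limits are self-report by unblinded patients, recall (longest at M4), and missing answers from those who withdraw. The last is serious here, because the sample size allows for 50% withdrawal or replacement and some patients may leave because of harm.
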